| Tan et al described that with oral 20mg methylprednisolone monotherapy in IGM, 80.7% of patients responded well to steroid treatment. The rationale for a lower starting dose of oral prednisolone of 20mg for Asians is due to higher risk of developing side effects to steroid as compared to their Caucasian counterparts. For this study, 20 mg of prednisolone will be prescribed daily for first 2 weeks, followed by tapering doses of 15mg daily over 2 weeks, then 12.5 mg daily for 2 weeks, proceeding to 10 mg daily for 2 weeks, subsequently taking 7.5mg daily for 2 weeks and lastly 5mg daily for 2 weeks (refer to Figure 2). 20mg of omeprazole is to be taken together with prednisolone. (Refer to Section 8.6 on justification for omeprazole).  Postolva et al described that with oral methotrexate monotherapy (starting dose of 10-15mg/week and increased to 20-25mg/week given orally or subcutaneously) in IGM, 94% had disease improvement^16^. Only oral formulation of methotrexate was chosen in our study to standardize the bioavailability and ease of administration in this trial^17^. In this study, 10mg of methotrexate will be prescribed to be taken once a week for a month and increased to 15mg of methotrexate to be taken once a week for another two months. 5mg of folic acid is to be taken together with methotrexate once a week (Refer to Section 8.6 on justification for folic acid).  *Modification of doses*  Modification of doses may occur during the study period and this will be dependent on patient’s clinical response and the attending doctor’s judgement. Principal Investigator (PI) or Co-Investigators (Co-Is) may increase the methotrexate dosage from 15mg to 20mg and may increase the 5mg folic acid intake up to 6 times a week (except the day of taking methotrexate) to mitigate methotrexate’s side effect, if needed. |  |
| Rationale for Study Population |  |
| The reported incidence of IGM is around 2.4 per 100,000 women aged 20–40 years. The study team will be including women aged 21 to 60 years because IGM often affects women who are young to middle aged. In addition, any women below the age of 21 years are unable to give consent independently in Singapore. |  |
| Rationale for Study Design |  |

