| The risk anticipated for the patients are:  1. All research techniques and medications have potential dangers and adverse effects. Blood collection may result in discomfort, bleeding, bruising, or swelling where the needle was inserted. Fainting may occur, and infections happen infrequently.  2. Allergic reactions can occur with any drug such as rash, itching etc.  3. Rarely, a severe and possibly life-threatening allergic reaction can occur. Symptoms of a severe reaction include: swelling of the face, difficulty breathing, or a sudden drop in blood pressure that may cause dizziness.  4. For the study drugs, there are some side effects that are unique to the drugs (prednisolone and methotrexate).  i) Prednisolone may cause mood changes (confusion, depression), weight gain, fluid retention, nausea, vomiting, indigestion, easy bruising, blood or black, tarry tools, blurred vision, increased urination or thirst, muscle weakness or cramps and severe stomach pain.  ii) Methotrexate may cause mouth ulcers, nausea, vomiting, abdominal pain, diarrhoea, rash, hair loss, easy bruising, severe sore throat, tiredness, paleness, yellow eyes, tea-coloured urine, constant abdominal pain, risk of infection and breathlessness or persistent dry cough. |  |
| **STUDY POPULATION** |  |
| List the number of subjects to be enrolled |  |
| 40 IGM patients, aged between 21 to 60 years will be recruited from NUH. |  |
| Criteria for Recruitment |  |
| Patients must have undergone biopsy and diagnosed with IGM. Eligible patients will be informed by their attending healthcare professional on the study during the clinic session. If patient is interest to join the study, a qualified study team member will then explain the study and obtain informed consent from the patient. Before beginning any study-related procedures, informed consent will be obtained. Patient will then be assigned a participant study code and randomised to a treatment arm. Recruitment will be done face-to-face in NUH at Breast Care Centre. |  |
| Inclusion Criteria |  |
| Patients will have to meet all of the following criteria below:   - Women, aged between 21 and 60 years - Positive diagnosis of idiopathic granulomatous mastitis based on histopathology results - Willing and able to give informed consent |  |
| Exclusion Criteria |  |

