| *Screening*  After patient is consented to the study, a baseline blood test (32mls, including pregnancy test, Hepatitis B test, Hepatitis C test, full blood count, liver function test and renal function test) and chest X-Ray will be conducted during the baseline visit to assess for eligibility prior to enrolment to the treatment phase. Additional research blood (14.5mls, 1 tablespoons) will be collected at this baseline visit for research purposes. Patient may be exempted from chest X-Ray and/or blood test if patient has done the same test within 30 days.  Baseline demographics and relevant clinical variables of patients will be collected. The following demographic and clinical variables will be collected: age of presentation, pre-menopausal or post-menopausal status, parity / breastfeeding status, concomitant rheumatic conditions, personal or family history of tuberculosis, smoking or alcohol intake, presenting complaint, unilateral or bilateral involvement, affected quadrant of the breast, duration of symptoms and previous antibiotics prescription for treatment of IGM.  Information on comorbidities will be evaluated to ensure suitability for both treatment arms prior to recruitment. Examples include drug allergies, plans for pregnancy, ongoing infection, previous history of cancer, previous tuberculosis, epilepsy, diabetes, hypertension, kidney, liver, cardiac problems, osteoporosis, glaucoma, peptic ulcers, previous side effects to either prednisolone or methotrexate.  If patient fulfilled all the eligibility criteria after screening assessment, she will be randomised to either of the treatment arm.  If patient did not meet the full eligibility criteria (eg. Pregnant, hepatitis carrier or abnormalities in renal or liver panels), she will not proceed to the treatment phase. The data collected and additional blood samples will be kept for analysis.  *Treatment Phase*  Patient will be scheduled to attend a clinical visit (T_0_) to either breast or rheumatology clinic if she meets all eligibility criteria for the initiation of treatment dose. There will be a window period of ± 7 days for this clinical visit. Patient is required to complete a pre-treatment quality of life online survey (approximately 10-15 minutes).  Patient will be scheduled for blood test (8mls, 0.5 tablespoons) and clinical visits to either breast or rheumatology clinic at the 1^st^ (T_1_), 2^nd^ (T_2_), 3^rd^ (T_3_) and 6^th^ (T_4_) month to assess their signs and symptoms, and drug compliance. There will be a window period of ± 14 days for each of these clinical visits. Additional research blood (14.5mls, 1 tablespoons) will be collected on the 1^st^ (T_1_) and 6^th^ (T_4_) months.  Patients are required to undergo a breast ultrasound to assess for their radiological response during the 3^rd^ (T_3_) clinical visit. A window period of ± 14 days will be applicable. The initial measurement of the breast lesion or mass will be recorded in three dimensions – i.e. anteroposterior, superior-inferior, mediolateral measurements. If complete clinical and radiological complete response has been achieved on the 3^rd^ (T_3_) visit, the doctor will discontinue the drug in a safe manner and no further breast ultrasounds will be required. If the patient’s symptoms or signs have not resolved by the 3^rd^ (T_3_) clinical visit, patient’s drug dosage will be assessed by the rheumatologist and treatment may be continued up to the 6^th^ (T_4_) month period and a repeat breast ultrasound will be required at the 6^th^ (T_4_) month. If symptoms have not resolved by the 6^th^ (T_4_) month of clinical visit, the patient’s drug dosage may be up-titrated or will be given an addition of a second therapy, i.e. combination therapy of steroid and methotrexate may be used. For clinical visits mention above, it will coincides with standard care visit.  During the clinical visits, Tingting Hu et al’s “M- score” will be adopted to grade the severity of the disease. M score is being calculated during clinical visits for IGM patients regardless of trial status for objective follow up. This is a common practice. For this study, the score will be administered by their attending healthcare professional (not limited to breast surgeons, investigators, or breast care nurses).  The M-score will be the sum of the following:  1) Mass score  2) Erythema score  3) Fistula score  4) Pain score  5) Quality-of-life (QoL) score  The scoring criteria were defined as follows:  1) Mass score: 0 for the absence of mass by palpation; 1 for mass ≤3 cm by palpation; 2 for mass >3 cm by palpation.  2) Erythema score: 0 and 2 for the absence and presence of erythema, respectively  3) Fistula: 0 and 2 for the absence and presence of fistula, respectively  4) Pain Score: 0 for Visual Analogue Score (VAS) 0-2; 1 for VAS 3-5; 2 for VAS 6-10  5) QoL score: 0 for absence of effects on QoL; 1 for mild effects on QoL, where the patient does not require medical assistant; 2 for serious effects on QoL, where the patient requires medical assistant  The total M-score ranges between 0 and 10 and serves as a quantitative and objective measurement of the severity of the symptoms.  The primary endpoint will be the clinical complete response (cCR) rate, which is defined as the proportion of patients who have an M-score of ≤ 1 at ≤1 years after treatment.  The secondary endpoints will be as follows:   - - The time to cCR, defined as the median time to cCR post randomisation.   - The treatment failure (TF) rate, defined as the proportion of patients with TF at 1 year post randomisation. The TF status will be defined as follows:     - If the patient has an M-score ≥6 before randomisation, TF is defined as the M-score remaining at ≥6 at 1 month post randomisation.     - If the patient has an M-score between 4 and 5 before randomisation, TF is defined as the M-score remaining at ≥4 and never being lower than 4.     - If the patient has an M-score <4 at baseline but never reaches cCR after randomisation, TF is defined as the M-score being >5 at the follow-up and remaining above 5 for one month. - Relapse rate, which is defined as the proportion of patients who have M-score >4 among the patients who achieved CR.   Throughout the course of the study, there are possible flares and relapse of the disease. Flares will be defined as any increase in M-score or lesion size on ultrasound whilst on therapy. While relapse will be defined as recurrence of symptoms or signs of IGM in the breast after previously experiencing complete resolution following therapy. If relapse occurs, patient will restart the same treatment arm for 6 months.  In the event of flares, blood test (8mls, 0.5 tablespoons) and additional research blood (14.5mls, 1 tablespoons) will be collected and the allocated treatment for the patient will be up-titrated by the doctor. In event of relapse, treatment for the patient will be reinitiated as per the allocated arm.  Additional research blood samples collected during the trial will be used for gene expressing profiling to identify unique patterns of gene expression that can be used to diagnose IGM and predict its treatment response.  Regardless of treatment arm, patient will be monitored by either breast surgeon or rheumatologist. Surgeons will assess for eligibility into trial, clinical reviews, and ultrasound breasts interpretation. Rheumatologists will be monitoring for drug side effects and titration if required. In event of failure of medical therapy, surgeons will have to intervene accordingly for aspiration or surgical drainage. In the event where patients require aspiration or surgical drainage during the study, methotrexate or prednisolone should be continued unless there is evidence of sepsis. The frequency of aspiration or surgical intervention will be recorded as events during the study.  Whenever the disease has been resolved during the study period, the balance medication and/or packaging will be retrieved to do medication accounting and checking for adherence to assigned treatment arm.  If side effects were to develop, doctors will evaluate the severity of the side effects and withdraw the patients from the trial if needed. |  |

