| De-identified blood samples will be analysed and stored in NUH Tissue Repository. Recruitment and follow-up survey data will be collected electronically via NUHS REDCap. Only study team members with delegated rights will be able to access the data under the supervision of PI and Site-PI. All survey data will be collected electronically via FormSG. A copy of de-identified data will be stored in a secured server at NUH. |  |
|  |  |
| **SAMPLE SIZE AND STATISTICAL METHODS** |  |
| Determination of Sample Size |  |
| The prevalence rate of IGM in NUH is currently at 10 to 15 patients per year. Based on a stepped rule of thumb, a minimum sample size of 30 will provide at least 80% power to detect a medium standardised effect size of between 0.3 to 0.7 based on a randomised two-group comparison (Machin et al, 2021). Assuming a 20% attrition rate, the sample size required for this study is 36 patients. This will be rounded up to a sample size of 40 patients over a period of 36 months. |  |
| Statistical and Analytical Plans The primary outcome of 6-month clinical or radiological complete response will be compared between arms using Chi-square test. The effect estimate will be quantified in terms of difference in proportion as well as relative risk (RR) and their associated 95% confidence interval (CI). The secondary outcomes of time-to clinical or radiological response and time-to-relapse will be evaluated via the Kaplan-Meier method. The differences in survival curves will be compared using log rank test, with the effect estimate quantified in terms of hazard ratio and its 95% CI. The primary analysis of this trial will be based on Intention-to- Treat (ITT). A Per Protocol (PP) analysis will be performed on all patients who have completed 6 months of treatment regimen as a sensitivity analysis.  Chi square test will be used to evaluate the proportion of side effects and requirement for percutaneous or surgical intervention during treatment between arms. Modified Poisson regression will be used to identify clinical or biomarkers that are associated with treatment response and quantify the effect in terms of RR.  Patient reported outcomes will be reported via a survey on FormSG, conducted online. The questions will be adapted from SF36 V1 Singapore version and EORTC-BR23. Below are the domains to be compared:   - - General Health   - Physical Health   - Mental Health   - Body Image   - Sexual Image   - Breast Health |  |
| **ETHICAL CONSIDERATIONS** |  |

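### In 40 patients, the usual modified Poisson test will too often declare an uncommon binary factor associated with response when response is high

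*Protocol*

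**What the plan says.** Section 11.2 of the protocol names the method for the predictor analysis: "Modified Poisson regression will be used to identify clinical or biomarkers that are associated with treatment response", with the effect expressed as RR. This serves the third secondary objective in section 2.3, potential predictors of response, which gives IL-6, CRP and the neutrophil-to-lymphocyte ratio as examples.

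Section 6.3 (Screening) lists the clinical variables collected at baseline. Several are naturally yes/no, for example "concomitant rheumatic conditions, personal or family history of tuberculosis, smoking or alcohol intake"; menopausal status and unilateral or bilateral disease are also listed. The protocol gives no prevalence for any of them.

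The sample is small. Section 3.1 says "40 IGM patients, aged between 21 to 60 years will be recruited from NUH", and section 11.1 assumes 20% attrition.

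No expected 6-month complete response rate is stated. The background sections cite published results: a complete response of up to 75% with methotrexate (section 1), and "80.7% of patients responded well to steroid treatment" (section 1.2, dose rationale).

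**The concern.** Modified Poisson regression is a log-link Poisson fit with a sandwich variance built from the residuals. It is sound in large samples. In a small group where everyone responds, the fitted value equals the outcome for each patient, the residuals are zero, and the sandwich treats that group's response rate as known without error. Two, three or four such patients then look equally certain.

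The null hypothesis of interest is that the factor is unrelated to response. In the all-responder pattern the test asks something else: whether response among patients without the factor is below 100%. At high response rates that is nearly always so, and the pattern arises often by chance in a group of four to eight patients.

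At stake is the list of predictors that the trial reports. Section 1.2 (study design rationale) hopes to personalise drug choice. A factor with no real association could be reported with a confidence interval that excludes 1.

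**Working it through.** **Inputs from the protocol.** N = 40 (sections 3.1 and 11.1). Attrition is 20%, so 40 × 0.8 = 32 evaluable. Method: modified Poisson with RR (section 11.2).

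**Inputs assumed.** Two-sided 5%, because no alpha is stated and section 11.2 uses 95% intervals for the main comparison. Number of patients with the factor (carriers): 4, 6, 8 or 12 of 40. True response: 50% to 80.7%, the same with and without the factor.

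**The plan's own figure.** Section 11.1 says "Assuming a 20% attrition rate, the sample size required for this study is 36 patients". From the minimum of 30, 30 × 1.2 = 36 reproduces it (30/0.8 = 37.5 would give 38). The total is then rounded up to 40, which is used below.

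**Formula.** For one binary factor, with n1 carriers responding at rate p1 and n0 others responding at rate p0:

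- log RR = ln(p1/p0)
- robust variance = (1 − p1)/(n1 p1) + (1 − p0)/(n0 p0)

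A fitted Poisson GLM with sandwich covariance agrees with this closed form. If p1 = 1 the first term is zero, and z = −ln(p0) / √[(1 − p0)/(n0 p0)]. The number of carriers then enters only through n0 = 40 − n1.

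**Worked case: 4/4 against 27/36.**

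- p0 = 27/36 = 0.75; ln(1/0.75) = 0.2877, so RR = 1.33.
- Variance = 0 + 0.25/(36 × 0.75) = 0.00926; SE = 0.0962.
- z = 0.2877/0.0962 = 2.99, p = 0.0028.
- 95% CI = exp(0.2877 ± 1.96 × 0.0962) = 1.10 to 1.61.
- Same data: chi-square p = 0.26, Fisher p = 0.56.

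With one carrier fewer, 3/3 against 28/37 also gives p = 0.0028, while Fisher gives p = 1.0.

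**How often this happens.** When all 4 carriers respond, the Wald test is significant whenever 32 or fewer of the other 36 respond. For 32/36, z = 0.1178/0.0589 = 2.00; for 33/36, z = 0.0870/0.0503 = 1.73. At 75% response the chance that all 4 carriers respond is 0.75⁴ = 31.6%, and nearly all of those tables reject.

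**Exact type I error** comes from enumerating every pair of binomial outcomes at N = 40. Tables with no responder among carriers are counted as non-significant.

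| True response | 4 carriers | 6 carriers | 8 carriers |
|---|---|---|---|
| 50% | 7.9% | 7.2% | 5.2% |
| 60% | 13.1% | 7.6% | 5.7% |
| 70% | 24.0% | 12.1% | 7.2% |
| 75% | 31.3% | 17.6% | 10.3% |
| 80.7% | 39.7% | 25.3% | 16.1% |

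- In the same settings the chi-square test stays at about 3% to 6% and Fisher's test at or below about 3%. At 75% response, for 4, 6 and 8 carriers, chi-square gives 3.9%, 4.0% and 4.5%, and Fisher 1.8%, 1.8% and 2.5%.
- At 75% response with 4 carriers, all of the 31.3% comes from tables in which every carrier responds.
- With 12 carriers the error is 4.0%, 4.7%, 5.0% and 5.4% at 50%, 60%, 70% and 75% response, and 7.0% at 80%.
- With 32 evaluable patients at 75% response: 29.9% (4 carriers) and 16.4% (6).
- A simple degrees-of-freedom scaling of the sandwich leaves 30.6% (4 carriers, 75% response, N = 40). Adjusting for arm leaves about 28% (4 carriers) and 16% (6), by simulation.
- A roughly normal continuous marker gives about 6% by simulation.

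**The case against.** Several points on the other side have force.

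- **Response rate.** A reader might infer that the plan expects response of 75% or more. It does not say so. The 75% is a cited upper figure, and the 80.7% describes patients who responded well to a steroid, which is not complete response. If true complete response is 60% or lower, a marked excess is confined to about four carriers or fewer. This stands, and it is why the table starts at 50%.
- **Which factors.** Section 6.3 lists variables to be collected and does not name them as regression candidates. The only predictors named in section 2.3 are continuous, and for those no group has zero residual variance. This stands as a limit on scope. Section 11.2 nevertheless covers clinical factors as well as biomarkers, so yes/no factors are within its reach.
- **Skewed markers.** A reader might extend the criticism to skewed markers entered untransformed. Nothing says they will be, and transformation is ordinary SAP content.
- **Several factors at once.** A reader might add up the false positives over several factors. That would mix this fault with ordinary multiplicity: five valid independent tests at 5% already give 1 − 0.95⁵ = 23%.
- **The SAP could repair it.** The protocol does not spell out a Wald p-value or a selection rule, and an SAP not shown here might add a safeguard. That is possible, but the robust Wald test and interval are the usual output of the named method, and an SAP that simply follows section 11.2 inherits the fault.
- **Consequence.** This is a secondary, exploratory analysis in a pilot trial. The primary comparison uses a chi-square test and is unaffected. This stands.

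**Conclusion.** The concern holds for uncommon binary factors, up to about 8 of 40 patients, when response is about 70% or higher. There the usual modified Poisson test has a type I error of 7% to 40% against a nominal 5%. The excess is small at 50% to 60% response, except with about four carriers or fewer (13% at 60% with 4 carriers). Factors held by 12 or more of 40 are little affected at 75% response or below (about 5%), and the zero-variance mechanism does not touch IL-6, CRP or the neutrophil-to-lymphocyte ratio as continuous markers.

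The algebra and the worked case need no assumption about prevalence or the true response rate. The error rates rest on assumed prevalences, assumed response rates and a two-sided 5% level, none of which the protocol states. The documents do not support a claim that the whole predictor analysis is invalid. The change is worth making because it alters which clinical factors would be named as predictors.

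**What to change.** In section 11.2, keep RR as the effect measure and add three statements:

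- For binary factors, the p-value comes from Fisher's exact test or the chi-square (score) test.
- The 95% CI for RR in those factors is score-based (Koopman or Miettinen-Nurminen).
- No sandwich-variance interval or p-value for RR is reported for a factor level in which all or none of the patients respond.

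Modified Poisson may stay for continuous markers. Penalised regression or permutation tests are options, but this fault does not require them.

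The cost is a short paragraph of protocol or SAP wording, with no extra data. The downside is wider intervals and fewer nominally significant factors. In the worked case the p-value would move from 0.003 to 0.26 (chi-square) or 0.56 (Fisher).
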